### Data Storage

All data will be stored on a password-protected computer and central disk space. Data from the website will additionally be stored on password-encrypted servers. Only persons who are part of the research team will have access to the data. Multimedia Appendix 3 presents the data-management plan.

### Incentives

To encourage participants to fill out their diaries, draw lots will be given based on the number of questions answered. The intervention group and the waiting-list control group will have equal chances to win prizes (ie, gift vouchers of popular supermarkets).

## Results

Development of the website and the mobile app is complete. The randomized controlled trial started in January 2018. As participants can start the study at different times, we aim to complete all testing by July 2019. Important protocol modifications will be reported on Clinicaltrials.gov. The results of the study will be communicated via publications. For these publications, the American Psychological Association guidelines for authorship eligibility will be followed.

## Discussion

### Overview

Adopting an active lifestyle is key in the management of type 2 diabetes [3]. As the prevalence of adults with type 2 diabetes is increasing [1], self-management interventions that can be applied to large groups are welcomed. Online interventions have the possibility to reach many users at the same time and have shown to be effective in altering health behaviors, especially when they are theory based [4,9]. “MyPlan 2.0” is a theory-based website and mobile app for motivating and supporting adults with type 2 diabetes to be more physically active and less sedentary.

### Study Implications

This study will test the effectiveness of “MyPlan 2.0” for each phase of the behavior change process using a randomized controlled trial. More specifically, this trial will investigate whether the program can increase patients’ physical activity and decrease their sitting time. Furthermore, we will determine whether these potential changes are mediated by alterations in personal determinants for change and result in positive health outcomes. Through the diaries, we will gain more insight into patients’ daily struggles to adopt an active way of living. Finally, potential differences based on participants’ characteristics will be explored. Consequently, the implications of this study will contribute to the literature of both the theoretical and practical domain of eHealth and mHealth, targeting self-management in adults with type 2 diabetes.

This study design has several limitations. First, as the resources for this study are limited, we will not be able to collect a large sample size. Consequently, it might be more difficult to identify statistically significant intervention effects. This issue highlights the importance of preventing dropout from the intervention. Dropout will be prevented by sending reminders to participants who are not logging in for follow-up sessions on the website via emails and phone calls. Second, considering the important role of creating a feeling of “goal-ownership” in self-regulation theory, participants can freely choose between the components increasing physical activity and decreasing sedentary behavior. We can therefore not ensure that the two components will have the same number of users. As a result, it might be more difficult to detect an effect for sedentary behavior if a large group selects physical activity as their target behavior and vice versa. As the structure of the intervention and the implemented behavior change techniques are exactly the same for both target behaviors, we decided to perform the analysis with one, rather than two, intervention groups. However, the selected behavior will be added as a moderator to the analysis. Third, in order to test our hypotheses, participants will need to fill out many questionnaires. This might cause higher levels of attrition. Fourth, participants are called weekly by the researchers to check for hypoglycemia or alterations in medication and to assess participants’ personal determinants for change via an interview. Due to these weekly phone calls, participants might show higher levels of engagement with the intervention than they normally would. However, as we will also implement these weekly calls in the control group, we believe that the calls will have a limited impact on the intervention effects. Finally, as the researcher who will analyze the data will also be involved in the data-collection process, blinding of the data analyst is not possible. To account for this issue, a strict protocol has been developed for processing and analyzing the data.

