### Study Design

A two-arm superiority randomized controlled trial will be performed. The study flow is depicted in Figure 1. Data will be collected during three home visits. During the first home visit, written informed consent will be obtained from the participants, and the participants will be asked whether they would like to increase their physical activity or decrease their sitting time. Participants will then complete questionnaires on physical activity, sedentary behavior, personal determinants for change (eg, self-efficacy), and health-related outcomes. Furthermore, participants’ weight and waist circumference will be assessed. Finally, participants from both groups will wear an accelerometer for a period of 10 days and fill out a morning and evening diary on each of these days. The diaries will assess participants’ daily goals and possible person-related barriers (ie, fatigue, stress, depressed mood, pain, nausea, and feelings of numbness or tingling in limbs).

After this period, LP will randomly allocate participants to the waiting list control group or the intervention group in a 1:2 allocation ratio by using an automated randomizer [18]. This will be done independent from patients’ choice to increase their physical activity or decrease their sitting time. Participants allocated to the intervention group who chose to increase their physical activity will be directed to the website targeting physical activity, whereas participants who chose to decrease their sitting times will be directed to the website targeting sedentary behavior. Participants owning a smartphone will be asked to download the mobile app. The website part of the intervention consists of five consecutive modules (a start module and four follow-up modules) spread over a 5-week period. Each week, participants from both groups will be phoned by a researcher. During these phone calls, questions regarding participants’ personal determinants for behavior change (eg, self-efficacy) will be repeated. In doing so, we will achieve the temporal separation needed to investigate causal pathways [19]. Furthermore, the phone calls will be used to check whether patients had hypoglycemia or made changes to their medication.

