### Hypotheses

Our primary hypotheses for this study are as follows: (1) The intervention group allocated to the module “Physical Activity” will show an increase in total physical activity from pre- to posttest compared to no change in the control group. This effect will be sustained in the intervention group from the posttest to the follow-up test. (2) The intervention group allocated to the module “Sedentary Behaviour” will show a decrease in sedentary behavior from pre- to posttest compared to no change in the control group. This effect will be sustained in the intervention group from the posttest to the follow-up test.

Our secondary hypotheses are as follows: (1) Positive changes in physical activity or sedentary behavior will be mediated by increases in the personal determinants self-efficacy, action planning, and coping planning. (2) The intervention group will have more positive health outcomes (ie, a lower weight; smaller waist circumference; and lower levels of fatigue, anxiety, and depression) from pre to follow-up test. (3) The negative effect of daily stressors (ie, fatigue, stress, depressed mood, pain, nausea, and feelings of numbness or tingling in limbs) on physical activity and sedentary behavior will be smaller in the intervention group from pre- to posttest compared to no change in the control group. This effect will be sustained in the intervention group from posttest to follow-up test.

As moderation analyses for online interventions targeting adults with type 2 diabetes are not usually performed [5], no hypotheses regarding the moderation effects are made. The following factors will be examined as potential moderators: age, sex, education, and chosen behavior (ie, physical activity or sedentary behavior).

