“MyPlan 2.0” consists of a website and a mobile app. The website, created using LifeGuide [30], is the basis of the intervention and has five consecutive parts. The first time a user logs into the website, (s)he can choose whether (s)he would like to be more physically active or less sedentary. The further structure of the website is independent of the chosen health behavior. First, in order to provide tailored feedback and personalized information (eg, the age and sex of the persons in the success stories are tailored to the user’s age and sex), all users answer questions assessing demographic information. Subsequently, users have the option to take a quiz regarding the benefits of the selected health behavior. Next, users fill in a questionnaire to assess their current levels of physical activity or sedentary behavior and receive feedback regarding the time they spend being physically active or sitting. Thereafter, users create a specific plan for increasing their physical activity (eg, “On Monday morning I will walk 10 minutes in the neighbourhood”) or decreasing their sedentary behavior (eg, “I will stand when talking on the phone”). Users will then state possible barriers for the selected goal, search for solutions, and decide how they will monitor their goal. Offered choices are a calendar, a booklet, the mobile app, etc. Next, users will see an overview of their goals, barriers, and solutions and how they will monitor their behavior change: This is called the action plan. Finally, users will be offered additional information about how they can receive social support from their environment.

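### Each primary hypothesis concerns one module, but the analysis pools the modules and names no module-specific contrast as the primary test

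*Protocol article*

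**What the plan says.** In the protocol article, the Hypotheses section gives two primary hypotheses, each for one module and its own outcome. The first reads "The intervention group allocated to the module “Physical Activity” will show an increase in total physical activity from pre- to posttest" and sets this against no change in the control group. The second reads "The intervention group allocated to the module “Sedentary Behaviour” will show a decrease in sedentary behavior from pre- to posttest", with the same comparator.

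Under Study Implications, the limitations paragraph says "we decided to perform the analysis with one, rather than two, intervention groups". The reason given is that the structure and the behaviour change techniques are the same for both targets. The next sentence is "However, the selected behavior will be added as a moderator to the analysis". The Hypotheses section lists chosen behaviour beside age, sex and education as a potential moderator and states that "no hypotheses regarding the moderation effects are made".

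The Participants section sizes the trial at 96 (64 intervention, 32 control) for two groups and three measurements, with no split by module.

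The choice of behaviour appears in two places. Study Design places it at the first home visit, before randomisation and in both arms: "participants will be asked whether they would like to increase their physical activity or decrease their sitting time". Description of the Intervention places it at login: "The first time a user logs into the website, (s)he can choose whether (s)he would like to be more physically active or less sedentary".

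**The concern.** The group-by-time effect from a pooled intervention arm is a weighted average of two effects: that in participants directed to the website for the outcome being analysed, and that in participants directed to the other website. It equals the effect in hypothesis 1 or 2 only if each module changes the other behaviour as much as its own.

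Two misreadings could follow. A null pooled result for sitting time could hide a sedentary module that works. A positive pooled result for physical activity could not be credited to the physical activity module. The only term that separates the modules is the moderator, and the plan attaches no hypothesis to it. At analysis there would be two candidate results for each primary hypothesis, with nothing to say which one decides it.

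**Working it through.** **1. Hypothesis against test**

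| | Hypotheses section | Pooled main effect |
|---|---|---|
| Physical activity | Physical activity module versus control | Both modules versus control |
| Sedentary behaviour | Sedentary module versus control | Both modules versus control |

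Let s be the share choosing the matching module, d the on-target effect, and k the off-target effect as a fraction of d. The pooled effect is

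s·d + (1 − s)·k·d.

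For s below 1 this equals d only when k = 1. The documents give neither s nor k; the limitations paragraph says that equal numbers cannot be ensured.

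**2. The plan's own figure**

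Inputs from Participants: effect size 0.37 (metric not stated), alpha .05, a stated beta of .90 read here as power .90, two groups, three measurements, correlation not stated. With a repeated-measures F test and correlation 0.5, f = 0.37 gives N = 54 (between groups) or 18 (group-by-time). Reading 0.37 as d (f = 0.185) gives 207 or 64. Among the between-group and group-by-time settings tried, 96 was reached at 90% power only for the group-by-time test with f = 0.185 and a correlation of about 0.21 to 0.26. The figure therefore cannot be confirmed from the stated inputs. That is a separate matter. To keep it out of this point, the next step takes the planned 90% as given.

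**3. Pooled test against within-choice test**

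Calibration: with a two-sided t test at .05 and 64 versus 32, 90% power needs a standardised effect of 0.709 on the analysis scale. The standard error is √(1/64 + 1/32) = 0.217. The within-choice contrast keeps the full effect but uses 64s versus 32s participants, assuming that the 2:1 ratio holds within each choice group. At s = 1/2 its standard error is √(1/32 + 1/16) = 0.306.

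At s = 1/2 the pooled effect is 0.709 × 0.5 = 0.355 with k = 0, and 0.709 × (0.5 + 0.5 × 0.5) = 0.532 with k = 0.5.

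| Share choosing matching module | Pooled, k = 0 | Pooled, k = 0.5 | Within choice, same-choice controls |
|---|---|---|---|
| 1/3 | 19% | 58% | 45% |
| 1/2 | 37% | 68% | 62% |
| 2/3 | 58% | 77% | 75% |
| 0.8 | 74% | 83% | 83% |

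**4. Where the two tests cross**

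Ignoring the change in degrees of freedom, powers are equal when s + (1 − s)k = √s, so k = √s/(1 + √s). For s = 1/2 this is 0.707/1.707 = 0.41. Over the shares in the table, the crossing lies at about 0.35 to 0.46. Below it the within-choice test has more power; above it the pooled test does.

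**5. Is a within-choice contrast a randomised comparison?**

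Yes, if choice means the answer at the first home visit. Study Design obtains that answer from all participants before allocation and makes allocation independent of it, so each choice group has its own randomised controls. Comparing one module's users with all controls would not have this property.

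**The case against.** Four arguments favour the plan.

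*The model already contains the answer.* With selected behaviour as a moderator, and moderation tested by interaction terms (Statistical Analysis), module-specific effects can be estimated. This stands, and it narrows the point. A reader might infer that the trial cannot test its primary hypotheses at all; the documents do not support that. What is missing is a statement that these contrasts are the primary tests.

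*Pooling is reasoned, disclosed and suited to the programme-level aim.* Study Implications asks whether the programme changes activity and sitting time, and the pooled effect answers that. The authors also concede that an effect on the less-chosen behaviour will be harder to detect. This stands as a reason to report the pooled effect. Shared structure and techniques do not imply equal effects on a given outcome, though, and disclosure does not make the test match the hypotheses.

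*The power loss may not exist.* A reader might infer that pooling must cost power, for instance that it halves an effect of 0.37 and leaves 16% power at a 50:50 split. That figure assumes no off-target effect and baseline adjustment with correlation 0.5. Under those settings even an undiluted effect has only about 50% power at 64 versus 32, so the 16% mixes dilution with the separate sample-size question. With a half-size off-target effect, the pooled test has slightly more power than the within-choice test at an even split. This objection stands.

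*The two descriptions of the choice scarcely conflict.* A reader might infer that the moderator is a post-randomisation variable seen only in the intervention arm. Study Design governs the trial and has participants directed to the website matching their earlier answer. Description of the Intervention explains how the website works for a user, and nothing says that the login answer will define the analysis variable. One clarifying sentence is enough.

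**Conclusion.** The point holds as a mismatch between the primary hypotheses and the primary test. The pooled group-by-time effect is the quantity stated in neither hypothesis unless off-target and on-target effects are equal, which the documents do not claim. The contrasts that match the hypotheses are available from the planned model but are not designated, and the stated 90% power was not derived for them.

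The size depends on the split and the off-target effect, both assumed here. Taking the planned 90% as given, an even split yields pooled power between 37% (no off-target effect) and 68% (half-size), against 62% within choice. A loss of power from pooling is therefore possible but not established, and the conclusion does not depend on it: a more powerful test of a different quantity still does not test the stated hypotheses.

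**What to change.** From the planned model, with group, time, choice and their interactions, name two primary contrasts:

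- Hypothesis 1: group-by-time effect on total physical activity among participants who chose activity, against controls who made the same choice.
- Hypothesis 2: group-by-time effect on sedentary time among participants who chose to sit less, against controls who made the same choice.

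Then:

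- define choice by the answer at the first home visit, and state that the login choice does not define the analysis variable;
- report the pooled effect as the programme-level result;
- state how multiplicity is handled for the two primary tests;
- state that the 90% power does not apply to the within-choice contrasts, and give their power over a range of splits.

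If the sponsor prefers to keep the pooled test as primary, the alternative is to restate both hypotheses for the pooled intervention group.

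Either route changes only wording, since choice is already recorded in both arms before randomisation. The price of the first is a less favourable stated power: about 62% per contrast at an even split on the calibration above, before any multiplicity adjustment. The price of the second is giving up module-specific primary claims.

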## Appendix

Multimedia Appendix 1 Completed SPIRIT checklist. SPIRIT: Standard Protocol Items: Recommendations for Interventional Trials.

Multimedia Appendix 2 Screenshots from the website and the mobile app.

Multimedia Appendix 3 Data management file.

## Abbreviations

eHealth: electronic health
HAPA: Health Action Process Approach
IPAQ-L: long International Physical Activity Questionnaire
LASA: Longitudinal Aging Study Amsterdam
mHealth: mobile health
PROMIS: Patient-Reported Outcomes Measurement Information System
SPIRIT: Standard Protocol Items: Recommendations for Interventional Trials
